### Sample size

The sample size has been calculated based on the detection of a difference in effectiveness compared with the non intervention group (NIG). It has been calculated by multiplying the size of a simple randomised design by the design effect or factor of inflation. For the simple randomised design, on accepting an alpha risk of 0.05 and a beta risk of 0.20 in a bilateral contrast, 59 subjects will be required in the first group and 59 in the second group to detect a difference greater than or equal to 28.4% in the screening coverage of the 41.6% in the NIG. The lost to follow up rate has been estimated at 20%. The calculation of the sample has been performed with the Granmo 5.2 computer programme for Windows. According to a review of the literature [23-25], considering an intraclass correlation coefficient of 0.05 and a mean number of 3,500 women from 30 to 70 years of age with incorrect screening by BHCA, the design effect will be 176 and thus, 20,768 women with incorrect screening will be required.

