### Design

Pragmatic, blinded, multicentre, randomised, controlled clinical trial with four branches, and a three years follow-up. The randomisation unit was BHCA.

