### Population

20,994 women from 30 to 70 years of age with incorrect screening criteria (data obtained from SPHCI) ascribed to the BHCA will be included in the study. Incorrect screening will be defined as [9]: 1.- No cytology in the last 3 years from women between 30 to 40 years, 2.- No cytology in the previous 5 years from women between 40 to 65 years, 3.- No previous cytology history for females older than 65 years or women who have not had their last cytology before the age of 60. The exclusion criteria will be: (a) hysterectomised women, with a current history of pre-malignant lesions (AGUS, ASCUS, LSIL, HSIL), carcinoma in situ and cervical-uterine cancer, HIV positive or other causes of immunosuppression (since these women follow a specific protocol); (b) those residing outside the study setting for more than 6 months; and (c) those ascribed to the study BHCA but with a physician assigned in an UBA of another zone different from the one considered in the study.

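### The 20,768 women required is a two-group total in a four-arm trial, its cluster size does not match the population, and one BHCA per arm cannot give the stated 80% power

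*Protocol article*

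**What the plan says.** All references are to the protocol article.

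- **Sample size.** The section sizes one comparison with the non-intervention group (NIG). The error rates are set "on accepting an alpha risk of 0.05 and a beta risk of 0.20 in a bilateral contrast". Before any inflation for clustering, the text states that "59 subjects will be required in the first group and 59 in the second group". The purpose given for this number is "to detect a difference greater than or equal to 28.4% in the screening coverage of the 41.6% in the NIG". Loss to follow-up is put at 20%. The clustering inputs are then introduced as "considering an intraclass correlation coefficient of 0.05 and a mean number of 3,500 women from 30 to 70 years of age", where the 3,500 is a count per BHCA of women not correctly screened. The section concludes that "the design effect will be 176 and thus, 20,768 women with incorrect screening will be required".
- **Design.** The study is a "randomised, controlled clinical trial with four branches", and the BHCA is named as the unit of randomisation.
- **Setting.** There are five BHCAs. Four are to be used because there are four study groups, so each arm is one BHCA.
- **Population.** The study will include "20,994 women from 30 to 70 years of age with incorrect screening criteria". The Abstract (Methods/Design) places these 20,994 women in four BHCAs. It also describes the patients themselves as being distributed at random to the groups.

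**The concern.** A reader who sees 20,768 required and 20,994 available will conclude that the trial is adequately powered. That conclusion needs three things: that 20,768 covers all four arms, that the design effect was built on the BHCAs actually used, and that enrolling more women within a BHCA can offset the clustering. The protocol's own figures contradict all three.

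At stake is the power claim for the trial comparison of screening coverage. The uptake estimates from that trial also feed the cost-effectiveness model.

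**Working it through.** **Inputs.** From Sample size: 41.6% in the NIG, a difference of 28.4 points (hence 70.0%), two-sided alpha 0.05, beta 0.20, 20% loss, ICC 0.05, 3,500 women per BHCA. From Design and Setting: four arms, the BHCA as unit, four BHCAs. From Population and the Abstract: 20,994 women in those four BHCAs.

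**1. Reproducing the plan's figures.** Pooled-variance formula for two proportions, mean proportion (0.416 + 0.700)/2 = 0.558:

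n = [1.960 × √(2 × 0.558 × 0.442) + 0.842 × √(0.416 × 0.584 + 0.700 × 0.300)]² / 0.284² = 46.8, so 47 evaluable per group.

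- Allowing for loss: 46.8 / 0.8 = 58.5, rounded up to 59. This matches.
- Design effect: 1 + (3,500 − 1) × 0.05 = 175.95, rounded to 176. This matches.
- Total: (59 + 59) × 176 = 118 × 176 = 20,768. This matches exactly, so only two groups are counted.

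**2. Two groups against four arms.** Each group needs 59 × 176 = 10,384 women, and 10,384 / 3,500 is about 3 BHCAs per arm. The trial supplies 20,994 / 4 = 5,248.5 women per arm, about half, in one BHCA.

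**3. Cluster size.** Four BHCAs of 3,500 would hold 14,000 women, not 20,994. The mean implied by the population is 5,248.5, and the design effect at that size is 1 + 5,247.5 × 0.05 = 263.4.

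**4. What one BHCA per arm delivers.** Effective n per arm = m / [1 + (m − 1) × ICC]. As m grows this approaches 1/ICC, which is 20 at ICC 0.05.

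| Women in the arm's BHCA | Design effect | Effective n | Nominal power, 41.6% vs 70.0% |
|---|---|---|---|
| 3,500 | 175.95 | 19.89 | 43.5% |
| 4,199 (5,248.5 less 20% loss) | 210.9 | 19.91 | 43.5% |
| 5,248.5 | 263.4 | 19.93 | 43.6% |
| 10,384 | 520.2 | 19.96 | 43.6% |

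Power is about 44% in every row, against the 47 evaluable women needed for 80%. Correcting 3,500 to 5,249, or tripling the women within a BHCA, changes almost nothing. The limit is the single cluster per arm. On the same approximation, the difference detectable with 80% power is about 42 points, not 28.4.

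**5. Dependence on the ICC** (m = 5,248.5, one BHCA per arm).

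| ICC | Effective n | Nominal power |
|---|---|---|
| 0.05 (protocol) | 19.9 | 44% |
| 0.03 | 33.1 | 65% |
| 0.02 | 49.5 | 82% |
| 0.01 | 98.1 | 98% |

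Only the first row uses the protocol's value. The others are assumptions that show the range.

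**6. If women were randomised individually.** No design effect would apply. With 5,248.5 × 0.8 = 4,199 evaluable per arm, the difference detectable at 80% power is about 2.80 × √(2 × 0.416 × 0.584 / 4,199) = 0.030, or 3 points.

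**The case against.** **The section only promises a comparison with the NIG.** That is so, and no comparison among the interventions is sized. But each comparison with the NIG still calls for 10,384 women per arm on the section's own arithmetic and gets about 5,249, so the objection does not rescue the figure.

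**The true ICC may be lower than 0.05.** At 0.02 the nominal power would exceed 80%. This limits how precisely the shortfall can be stated. The protocol nevertheless adopts 0.05 and builds its requirement on it, so its own claim fails on its own input.

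**The planned analysis is a Markov cost-effectiveness model with deterministic sensitivity analysis, and the article sets out no hypothesis test.** This softens the consequence. It does not remove it, because the sample size section states alpha and beta, and the model takes its efficacy inputs from the trial.

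**The Abstract speaks of patients being randomly distributed.** The Design section names the BHCA, the Limitations section refers to randomisation by groups, and a design effect is applied, so the cluster reading governs. If the Abstract were right, the design effect would be the error instead.

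Two stronger readings are tempting and not supported:

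- A reader might infer that the wrong total and the wrong cluster size cause the loss of power. Step 4 shows that they do not: with one BHCA per arm, power is the same at 3,500 and at 5,249.
- A reader might infer that the trial should recruit 4 × 59 × 176 = 41,536 women, or about 62,160 at the larger design effect (4 × 59 × 263.4). These products show the inconsistency but are not usable requirements. More women in the same four BHCAs add almost no information, and the setting has only five BHCAs against the roughly three per arm that the formula implies.

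**Conclusion.** The point stands. The stated requirement is a two-group total set against a four-arm population, and the assumed cluster size contradicts the population figure. Both are plain inconsistencies and need no outside assumption.

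The claim of 80% power is not met, because there is one BHCA per arm. At ICC 0.05 the nominal power for 28.4 points is about 44%. This rests on the protocol's ICC and effect size, roughly equal BHCA sizes, a normal approximation, and no adjustment for three comparisons with the NIG.

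The 44% should not be read as the trial's actual power. With one area per arm, between-area variance cannot be estimated and the arm effect cannot be separated from the area, so no valid cluster-level test stands behind the figure. It is best read as an optimistic nominal value.

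**What to change.** Rewrite the Sample size paragraph, without adding women:

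1. State that 20,768 is the figure for one two-group comparison and does not cover four arms. Do not replace it with 41,536 or about 62,160 as a corrected requirement.
2. Use the actual BHCA sizes in the design effect (about 263 at a mean of 5,249), or explain where 3,500 comes from.
3. Withdraw the 80% power claim. Report the nominal power of one BHCA per arm over a range of ICCs (about 44% at 0.05, 65% at 0.03, 82% at 0.02, 98% at 0.01), and say that arm and area are confounded.
4. Reconcile the Abstract with the Design section on the unit of randomisation. Only if women are in fact randomised individually, replace the calculation with one that has no design effect (about 3 points detectable with about 4,199 evaluable per arm).

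The cost is one rewritten paragraph and one reconciled sentence. The stated power becomes less favourable unless the unit of randomisation proves to be the woman.

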### Outcomes measures and statistical analysis

#### - Decision analysis

A Markov model will be developed to simulate the natural history of cervical-uterine cancer and to measure the impact, on costs and outcomes, of three different screening strategies. This same model of analytical decision has been used in several screening studies for cervical cancer [26-34]. The parameters of this model, clinical variables and costs, which would be included, are shown in the following sections of this protocol [35,36]. The population will be distributed across different health states of the model using transition probabilities over time. The temporal cycles of the Markov model will be 6 months of length during which time the state of health of the women may change or remain the same. These probabilities are conditioned to age, state of the HPV and history of the disease. The 11 states of health considered will be: healthy women, HPV infection, low grade intraepithelial lesion (L-SIL), high grade epithelial lesion (H-SIL), FIGO EIa stage invasive cancer (FIGOEla), FIGO EIb stage invasive cancer (FIGEIb), FIGO EIIa stage invasive cancer (FIGOEIIa), FIGO ELLb stage invasive cancer (FIGOEIIb), FIGO EIII stage invasive cancer (FIGOEIII), FIGO EIV stage invasive cancer (FIGOEIV), and death. These health states, recommended by the clinical experts of this study, are consistent with those extensively reported in the economic literature [26-34].

#### - Clinical effectiveness measures

The main effectiveness measures of this evaluation would be the total number of cytologies performed, HPV infections detected, lesions of different grades detected, episodes of cancer detected and the number of deaths avoided. The efficacy of the interventions will be obtained from the CRICERVA clinical trial.

#### - Costs measures

Micro-costing techniques will be used to estimate the health care costs of the different screening intervention of cervical cancer and treatments of different health states [37]. The costs will be presented in 2013 Euros (€) (year foreseen to finalize the study). Primary data of CRICERVA clinical trial will be used whenever possible. The costs will include the costs of: diagnosis, interventions and treatment for all women. The costs of diagnosis will include the cost of cytology, the HPV determination test and the control visit by the midwife or gynaecologist. The cost of the interventions will cover the cost of a full-time administrator, the personalized screening invitation letters, the informative leaflets and phone calls. The cost of treatment will depend on the state of health of the women but may include the costs of the visits to the gynaecologist, cytology tests, HPV determination, control visits with the physician, costs of radical hysterectomy, radiotherapy, chemotherapy, etc.

#### - Temporal horizon

The temporal horizon of the analysis will be the lifetime period of the woman.

#### - Discount rate

The discount rate to calculate costs and clinical outcomes will be 3% [22].

#### - Cost-effectiveness analysis

The cost-effectiveness analysis will be conducted comparing costs and effectiveness, measured in natural units, of the different alternatives to usual practice. In most cases the data will be obtained from the CRICERVA clinical study. The comparison will be performed using the Incremental Cost-Effectiveness Ratio (ICER) defined as the ratio of the difference in costs and the difference in effectiveness. The results will be expressed in terms of €/per unit of effectiveness.

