## Abstract

**Background:**

A high percentage of cervical cancer cases have not undergone cytological tests within 10 years prior to diagnosis. Different population interventions could improve coverage in the public system, although costs will also increase. The aim of this study was to compare the effectiveness and the costs of three types of population interventions to increase the number of female participants in the screening programmes for cancer of the cervix carried out by Primary Care in four basic health care areas.

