**Methods/Design:**

A cost-effectiveness analysis will be performed from the perspective of public health system including women from 30 to 70 years of age (n = 20,994) with incorrect screening criteria from four basic health care areas in the Valles Occidental, Barcelona, Spain. The patients will be randomly distributed into the control group and the three intervention groups (IG1: invitation letter to participate in the screening; IG2: invitation letter and informative leaflet; IG3: invitation letter, informative leaflet and a phone call reminder) and followed for three years. Clinical effectiveness will be measured by the number of HPV, epithelial lesions and cancer of cervix cases detected. The number of deaths avoided will be secondary measures of effectiveness. The temporal horizon of the analysis will be the life expectancy of the female population in the study. Costs and effectiveness will be discounted at 3%. In addition, univariate and multivariate sensitivity analysis will be carried out.

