**Discussion:**

IG3 is expected to be more cost-effective intervention than IG1 and IG2, with greater detection of HPV infections, epithelial lesions and cancer than other strategies, albeit at a greater cost.

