Due to the high prevalence of cervical cancer cases in this particular county we propose to launch a comparison of three different alternatives to improve the present coverage of the populational screening programmes in all the BHCA, therefore facilitating accessibility of population to the public health care system. The screening model proposed is centred on the recruitment of women with incorrect screening, performing cytology and the hybrid capture test for HPV to add diagnostic resolution due to the greater sensitivity of the test and the absence of screening in this population of women. Hence, systematic screening should be incorporated since these women have a greater risk of having cervical disease because of not having visited the health care system before. Therefore, this would facilitate earlier action in detecting pre-malignant lesions, helpingto t reduce the incidence of invasive cancer. To achieve so, the research team propose three different interventions, consisting in sending: (a) an invitation letter to participate in the screening; (b) an invitation letter and an informative leaflet; and, (c) an invitation letter, an informative leaflet and a phone call reminder. Therefore, there is: one common action in the three different interventions, which has been scientifically validated as effective, consisting in a personalized invitation letter sent by the primary health care professionals including a fixed appointment to undergo through a cytology test and, other two different interventions (informative leaflet and reminder call) to evaluate approaches for which there are few studies assessing the effectiveness of attendance to screening programmes. Following the indications of the National Health Care System to optimise the interventions of cancer prevention [18], the aim is to assess which is the most cost-effective intervention for a cervical cancer screening programme.

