## Method/Design

An economic evaluation of three populational screening strategies for cervical cancer will be performed. (Figure 1, 2) Particularly, a cost-effectiveness analysis will be conducted. These interventions will be compared to the current opportunistic screening strategy using data of the multicentre randomised trial (CRICERVA). The analysis will be conducted from the National Health Care System perspective [22].

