#### - Uncertainty

To study the uncertainty, an univariate and multivariate deterministic sensitivity analysis will be undertaken of the relevant parameters considered.

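### The article names usual practice as the only ICER comparator and plans no probabilistic uncertainty for the ICER, although its aim is to choose among three nested interventions

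*Protocol article*

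**What the plan says.** The Background of the protocol article ends with the objective: "the aim is to assess which is the most cost-effective intervention for a cervical cancer screening programme". The Abstract likewise sets out to "compare the effectiveness and the costs of three types of population interventions", and its Discussion paragraph states that "IG3 is expected to be more cost-effective intervention than IG1 and IG2", at a greater cost.

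The arms are nested. IG1 is the letter, IG2 adds a leaflet, and the Abstract gives "IG3: invitation letter, informative leaflet and a phone call reminder".

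On the comparator, Method/Design says "These interventions will be compared to the current opportunistic screening strategy". The Cost-effectiveness analysis section plans "comparing costs and effectiveness, measured in natural units, of the different alternatives to usual practice", with the ICER "defined as the ratio of the difference in costs and the difference in effectiveness". No ratio of IG2 to IG1 or of IG3 to IG2 is mentioned, and no rule for dominated strategies is given.

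On uncertainty, the article says that "an univariate and multivariate deterministic sensitivity analysis will be undertaken". The Statistical analysis section adds means, standard deviations and 95% confidence intervals for costs, and says that effectiveness, cost and ICERs will be reported for each alternative.

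**The concern.** With nested strategies, the decision is taken one component at a time: is the leaflet worth its cost once the letter is sent, and is the call worth its cost once both are sent? A ratio of IG3 to usual practice spreads the cost of all three components over the gain from all three. If the letter is cheap and effective, it can make a poor-value call look acceptable. Several strategies may also look acceptable against usual practice together, and the ratios alone do not say which to adopt.

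The second part concerns precision. The contrasts that decide the question are differences between interventions, and these are probably smaller than the difference from no intervention. A deterministic analysis shows how the ICER moves when inputs are changed. It attaches no probability to those changes, and the article states no interval for effects or ICERs. At stake is whether the trial's conclusion on the preferred strategy rests on the right contrast and comes with an honest statement of how sure it is.

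**Working it through.** **The plan's own figures.** The article gives no cost, no between-intervention effect and no ICER, so there is no economic figure to reproduce. The Sample size figures do reproduce and are not disputed here:
- Comparing 41.6% with 41.6 + 28.4 = 70.0%, two-sided alpha 0.05 and power 0.80 (pooled variance, no continuity correction), gives 47 per group. Then 47/0.80 = 58.75, rounded up to 59.
- Design effect = 1 + (3,500 − 1) × 0.05 = 175.95, about 176.
- 2 × 59 × 176 = 20,768.

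That calculation also concerns only the contrast with the non-intervention group.

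**Ratio against usual practice and sequential ratio.** All inputs here are assumed: extra cost in euros and extra women screened, per 1,000 women, relative to usual practice. With cost C and effect E, the ratio against usual practice is C/E. The sequential ratio is the difference in C divided by the difference in E from the next less costly strategy.

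| Set | Strategy | C | E | C/E | Sequential ratio |
|---|---|---|---|---|---|
| A | IG1 | 3,000 | 100 | 30 | 30 |
| A | IG2 | 4,500 | 110 | 40.9 | 1,500/10 = 150 |
| A | IG3 | 12,000 | 150 | 80 | 7,500/40 = 187.5 |
| B | IG1 | 2,000 | 200 | 10 | 10 |
| B | IG2 | 3,000 | 260 | 11.5 | 1,000/60 = 16.7 |
| B | IG3 | 6,000 | 300 | 20 | 3,000/40 = 75 |

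- For IG3, the sequential ratio divided by the ratio against usual practice is 187.5/80 = 2.3 in set A and 75/20 = 3.75 in set B.
- In neither set is a strategy dominated or extendedly dominated, and the order of the strategies is the same under both ratios. The two ratios can still lead to different decisions. In set A, at any value between EUR 80 and EUR 150 per extra woman screened, all three strategies pass against usual practice, yet neither the leaflet nor the call pays for itself.
- Range: in set B, with IG3 cost varied from 4,000 to 9,000 and IG3 effect from 270 to 340, IG3 against usual practice runs from 11.8 to 33.3. IG3 against IG2 runs from 12.5 to 600.
- At one corner of that range (cost 4,000, effect 340), IG3 against IG2 is 1,000/80 = 12.5, below the 16.7 of IG2 against IG1. IG2 is then extendedly dominated. The ratios against usual practice (10.0, 11.5, 11.8) do not show this on their face.

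**Sampling uncertainty.** The Design section makes the BHCA the randomisation unit, and the Setting section keeps four BHCAs for four groups, hence one per arm. Take the article's coverage of 41.6% in both arms (a simplification), 3,500 women per BHCA and the design effect of 176:
- SE of a difference between two arms = √(2 × 0.416 × 0.584 × 176/3,500) = 0.156. The 95% margin is 1.96 × 0.156, about ±31 points.
- Ignoring clustering: √(2 × 0.416 × 0.584/3,500) = 0.0118, a margin of about ±2.3 points.

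On the article's own ICC, the margin exceeds the 28.4 points planned against no intervention. When participation is the measure of effect, this uncertainty sits in the denominator of the ICER.

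**The case against.** A reader might infer that the plan cannot say which intervention is best, or cannot detect dominance. The article does not support that. It commits to reporting cost and effectiveness for each alternative, so the sequential ratios and both kinds of dominance follow by subtraction. The fault is that the stated analysis does not make this comparison.

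The sentence on usual practice could also be read as comparing the alternatives to usual practice among themselves, and the ICER definition is generic. Method/Design, however, says outright that the interventions are compared with current opportunistic screening, and no other comparator is named for the ICER.

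A journal article condenses a fuller protocol, and details of ICER ordering may be left to it. That would excuse silence. Here the article states a comparator in two places and expressly chooses a deterministic analysis, and these stated choices do not match the stated aim.

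A reader might also infer that sampling error and joint variation are ignored altogether. They are not: the multivariate analysis varies parameters together, and costs receive standard deviations and 95% intervals. What is absent is probabilistic weighting and any stated interval for effects or the ICER. A deterministic analysis is a legitimate choice in itself, so this half of the point asks for an addition and does not correct an error. Finally, the statement about IG3 is a prior expectation and should not be treated as an unsupported result.

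**Conclusion.** The point holds in limited form. The article specifies ICERs against usual practice as the only named comparator, while its aim is a choice among three nested interventions. It plans only deterministic sensitivity analysis for the ICER and states intervals for costs only. It therefore does not prespecify the comparison that its aim requires, nor how sure the answer will be.

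The size is unknown. The factors of 2.3 and 3.75 are illustrations on assumed inputs and are not estimates for this trial. They show that the two ratios answer different questions and can lie far apart. The ±31-point margin rests on the article's assumed ICC of 0.05, its figure of 3,500 women per BHCA and equal coverage of 41.6% in both arms. The point merits a change to the plan, but the data to be collected already permit the right analysis.

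**What to change.** In the Cost-effectiveness analysis section, order the four strategies (usual practice, IG1, IG2, IG3) by cost. Remove dominated and extendedly dominated strategies, and report sequential ICERs, each against the next less costly remaining strategy. Keep the ratios against usual practice as supplementary results.

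In the Uncertainty section, keep the deterministic analysis and add a probabilistic one. Draw participation, detection and costs jointly from distributions, and report an acceptability curve over a range of threshold values. With one BHCA per arm, between-BHCA variance is confounded with the intervention and cannot be estimated from the trial. It should be taken from the ICC of 0.05 assumed under Sample size and varied around that value. An acceptability curve built from woman-level variation alone would claim too much precision.

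The work uses the same model and the same trial data plus the external ICC, with no extra participants or visits. The cost is some additional programming, and the stated uncertainty will be wider.
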